## DISCUSSION

5

This study protocol describes the design of a randomized controlled trial with the following aims: (1) evaluate the relationship between user engagement and intervention efficacy, (2) investigate the efficacy of the application functions by investigating the relationship between usage time of the application functions and intervention efficacy, and (3) investigate the efficacy of the educational application compared to an active control application and to a wait‐list control group. To the best of our knowledge, this will be the first study to take behavioral data into account in the evaluation of the effectiveness of a complex alcohol reduction application on a large sample. Crane et al. (2018) recorded usage times in a factorial design study, with no significant differences between application components. They also found that application components in combinations led to improvements in alcohol‐related outcomes (Crane et al., 2018), supporting the conclusion of Webb et al. (2010), that effectiveness increases with the number of BCTs. Zhang et al. (2016) found in their self‐report study that notifications and information sharing were the most, while psychotherapy was the least useful feature of their mobile application. Attwood et al. (2017) observed mixed feedback regarding the usefulness of the individual features, which emphasizes the heterogeneity of user needs.

With an attempt of taking the continuously growing knowledge of the field into account, we developed a mobile application, Yoozan, with a wide range of functionality: self‐monitoring and feedback; action planning; normative feedback; identity change; community support; goal setting; evaluation of progress; and mood‐diary. We assume that functions/components in a complex application will compete for usage, resulting in different usage times in an ecologically valid context. By registering usage time of functions on the single‐user level, it is possible to examine application efficacy as a function of usage habits such as usage time, usage frequency, the number of used functions, and usage time of functions. This data will serve as useful guidance for future application development, helping to specify effective functions and user behaviors associated with high efficacy.

The following limitations of the protocol must be considered: (1) all measurements except behavioral data will be self‐reported that may be prone to biases (e.g., social desirability bias), (2) possible unequal group sizes leading to reduced statistical power due to the randomization process occurring before assessment for eligibility, (3) potentially there will be missing follow‐up data of the dropped outs, and (4) the application only available on Android operating smartphones.

Although mobile phones offer the potential to reduce the harms of hazardous drinking (Crane et al., 2015), up to date there have been relatively few studies conducted that evaluate the efficacy of evidence‐based smartphone applications aiming to reduce alcohol consumption (e.g., Crane et al., 2018; Gonzalez & Dulin, 2015; Zhang et al., 2016). By applying a randomized controlled trial, the results of the present study will be comparable with previous studies and will be informative about the overall efficacy of alcohol intervention applications. By investigating the behavioral correlates of the application, we hope that a more complex understanding of application efficacy will be achieved, making more focused intervention development possible in the future.

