**Methods:**

A randomized controlled trial will be conducted to determine the efficacy of a newly developed smartphone application compared to the controls in reducing alcohol consumption at a 30, 60, 90, 120, 150, and 180 days follow‐up. Hazardous drinkers, aged 18 years or older, will be recruited through web articles and will be randomized (blinded to their allocation), to receive one of the two versions of the application (educational or control application) for 30 days, or will be allocated to a wait‐list control group. Function usage times will be recorded on a single‐user level to determine the association between application usage and efficacy.

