### Recruitment of study participants and trial flow

2.2

Recruitment took place from December 2019 and is currently ongoing. Participants are recruited through promotion articles published on Hungarian Internet portals. In the articles, Yoozan is introduced with a call to participate in testing in case the reader wants to change his/her drinking habits. All interested participants are directed to the webpage of the study, from where the application can be downloaded. Based on a block randomization method, an equal number of participants download either Yoozan, the control application, or allocated to the wait‐list control group. After installing the application, participants are asked to read the participant information sheet and provide informed consent and a valid email address for which usability questionnaire and follow‐ups will be sent (see Figure 1).

Participants allocated to the wait‐list group are informed that 6 months later, the application will be sent to their email addresses and are encouraged to fill a few tests (7‐day Timeline Followback, Alcohol Use Disorders Identification Test [AUDIT]) with instant feedback.

Study inclusion criteria are informed consent via the Web form to ensure knowledge of procedures and the declaration of consent; participant age ≥18 years, to ensure a minimal age of participation; ownership of an Android‐operating smartphone and at least weekly Internet access, to ensure program access; a screening AUDIT score ≥8 out of 40, to include adults with potentially hazardous or harmful alcohol consumption; and an indication of an attempt to reduce alcohol consumption (screening motivation score ≥2 out of 5), to ensure a minimal willingness to change. Exclusion criterion is participation in other treatments for the reduction of alcohol consumption, to avoid confounding treatment effects.

The study targets Hungarian speaking users; thus, the language of the intervention is Hungarian. If the intervention is effective, translation to English and upload to App Store and Google Play is planned.

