## RESULTS

4

The composition of our sample will be demonstrated via descriptive statistics of participants' age, gender, and baseline 7‐day Timeline Followback, AUDIT measures, and motivation to change scores. Random imbalances between the intervention and control groups will be examined using chi‐squared tests. To evaluate the efficacy of the intervention, a repeated measure one‐way between‐groups analysis of covariance (ANCOVA) will be conducted. The analysis model will be built with group allocation as the independent variable, change in alcohol consumption as the dependent variables (the difference between baseline and follow‐ups 7‐day Timeline Followback in consumed alcohol units, binge drinking occasions, and drinking frequency), and age, sex, and motivation to change as covariates. Prior to the analysis, we will make sure that the specific assumptions for normality and homogeneity of variance for the one‐way ANCOVA will be met. In situations where data is missing—for example, with participants who are lost to the 6‐month follow‐up—the mixed model approach will be used to estimate missing values.

Multilevel modeling will be used to estimate the relationship between change in alcohol consumption (consumed alcohol units, binge drinking, and drinking frequency), application usage (total usage time, usage frequency, and usage time of functions) and application usability ratings in the educational and control application groups.

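### Allocation precedes consent, eligibility and baseline, leaving the wait-list contrasts open to selection bias, but the plan counts this only as unequal group sizes and lost power

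*Protocol article*

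**What the plan says.** Recruitment of study participants and trial flow (2.2) sends interested readers to the study webpage, where allocation decides what they receive: "Based on a block randomization method, an equal number of participants download either Yoozan, the control application, or allocated to the" wait-list. Consent is described next: "After installing the application, participants are asked to read the participant information sheet and provide informed consent". Wait-list members "are informed that 6 months later, the application will be sent to their email addresses" and, in the same sentence, are encouraged to fill in the 7-day Timeline Followback and the AUDIT. Registration and feedback (3.2) places the baseline measures in the registration step. Eligibility rests on what is reported there, including AUDIT of at least 8 and motivation of at least 2.

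The Discussion, in limitation (2), confirms the order in its own words and gives one consequence: "possible unequal group sizes leading to reduced statistical power due to the randomization process occurring before assessment for eligibility".

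On analysis, Results (4) says "Random imbalances between the intervention and control groups will be examined" with chi-squared tests. The outcomes are changes from baseline, and the covariates are age, sex and motivation to change. The abstract describes participants as "blinded to their allocation" in the sentence that introduces all three groups.

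**The concern.** Randomisation makes arms comparable among those who are allocated. Here the analysed sample consists of those who, after allocation, go on to consent, pass screening and give a baseline. If that step works differently by arm, the comparison is no longer protected by randomisation.

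The step does differ for the wait-list. App-arm members install an app and register inside it. Wait-list members learn that they will wait and are invited to complete tests. Both the decision to enter and the drinking they report can respond to that news. The reported drinking serves as part of eligibility and as the starting point of every change score.

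Unequal group sizes cost precision, and more recruits can make that good. Selection moves the estimate itself, and more recruits only make the wrong value more precise. A plan that names only the first leaves readers to treat the wait-list contrasts as ordinary randomised evidence. Calling any baseline imbalance random points the same way.

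**Working it through.** **1. Order of events**

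| Step | App arms | Wait-list | Where stated |
|---|---|---|---|
| Allocation | Before eligibility, at download | Before eligibility, at the webpage | 2.2; Discussion |
| Knowledge of allocation | Receive one of two app versions | Told of the six-month delay | 2.2 |
| Consent | After installation | Timing not spelled out | 2.2 |
| AUDIT and baseline drinking | At registration | Encouraged, with the delay known | 2.2; 3.2 |

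The two app arms pass through the same steps before their content differs. The wait-list does not.

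**2. The plan's own figure**

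Inputs from Sample size calculation (2.3): d = 0.20, power 80%, two-sided alpha 0.05. The noncentrality is d / √(1/n₁ + 1/n₂) with n₁ + n₂ − 2 degrees of freedom. The smallest equal group size giving power of at least 0.80 is 394 (power 0.8006), so the stated 394 per group reproduces.

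**3. The consequence the plan names: unequal sizes**

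Same formula, with 394 in one arm and a smaller wait-list (shares assumed):

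| Wait-list n | Share of 394 | Power at d = 0.20 |
|---|---|---|
| 394 | 100% | 0.80 |
| 355 | 90% | 0.78 |
| 315 | 80% | 0.75 |
| 276 | 70% | 0.72 |

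**4. The consequence it does not name: selection**

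None of these inputs is in the document; all are assumptions. Let u be a standard normal commitment trait that correlates r with reduction in drinking, with r = 0.2 to 0.3. The chance of completing baseline is 1 / (1 + exp(−(a + b·u))), with b = 0.5 to 1 and a set to give each arm's completion rate. With no true effect and no covariate adjustment,

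bias = r × (mean u among app-arm completers − mean u among wait-list completers).

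| Completion, app vs wait-list | Mean u, b = 0.5 | Mean u, b = 1 | Bias in SD, lowest to highest |
|---|---|---|---|
| 60% vs 50% | 0.189 vs 0.236 | 0.332 vs 0.413 | −0.01 to −0.02 |
| 60% vs 30% | 0.189 vs 0.333 | 0.332 vs 0.590 | −0.03 to −0.08 |
| 70% vs 30% | 0.143 vs 0.333 | 0.253 vs 0.590 | −0.04 to −0.10 |

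For the largest entry: 0.3 × (0.253 − 0.590) = −0.101. The sign is negative because the arm with lower completion keeps the more committed people, so here the wait-list looks better and Yoozan worse. If the wait-list completes more often, the sign reverses.

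**5. What such a shift would do at 394 per arm**

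| Shift | Two-sided rejection rate, no true effect | Power at true d = 0.20 if the shift opposes it |
|---|---|---|
| 0 | 0.05 | 0.80 |
| 0.05 SD | 0.11 | 0.56 |
| 0.10 SD | 0.29 | 0.29 |

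The last two entries coincide because 0.20 − 0.10 = 0.10.

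**The case against.** The strongest reply is about reach. The article ranks efficacy against controls as its tertiary aim. The engagement and function-use aims are modelled in the two app groups only, and Yoozan versus control app shares one entry route. That stands: what is exposed is the wait-list part of the tertiary aim. A reader might infer that the trial's main question is compromised; the document does not support that.

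Second, no differential entry is shown. The article gives no completion rates by arm, the timing of wait-list consent is inferred, and the flow chart is not available. This also stands: arms that can differ are not arms that do. But the order of allocation and eligibility is the article's own statement, so the risk itself is not inferred.

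Third, the plan already analyses change from baseline, adjusts for motivation and lists self-report bias as a limitation. This helps only in part. Baseline drinking and AUDIT are not covariates, and unmeasured commitment is untouched. The mixed model is aimed at missing follow-up, not at people who never gave a baseline.

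Fourth, it is tempting to say the blinding claim is false for the wait-list. The abstract's parenthesis can be read as attached to the two app versions, with the wait-list in a separate clause. On that reading there is an ambiguity to clear up, not an error.

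**Conclusion.** The concern holds for the wait-list contrasts. Limitation (2) draws an incomplete consequence from an order that the article itself states, and the analysis section treats any imbalance as random. The size and sign of the bias are unknown. The illustrated 0.01 to 0.10 SD rests wholly on assumed completion rates, selection strength and correlation, and it precedes any adjustment. The upper end, half of the targeted 0.20 SD, needs a 40-point completion gap together with the strongest assumed dependence.

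A reader might infer that the bias flatters Yoozan. The document does not support that: with lower wait-list completion the model gives a bias against Yoozan, and differences in how baseline drinking is reported could push either way. Yoozan versus control app and the engagement analyses are largely unaffected.

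**What to change.** 1. Make Yoozan versus control app the protected randomised efficacy contrast, and interpret wait-list contrasts as open to selection bias.
2. Add baseline 7-day consumption and AUDIT, both already collected, to age, sex and motivation as covariates. State that this cannot remove selection on unmeasured factors, nor reporting differences in a baseline given after the delay was known. Judge baseline differences by standardised differences; chi-squared tests do not suit age, AUDIT score or units consumed unless these are categorised.
3. Rewrite limitation (2) to name selection bias alongside power, and report by arm the numbers allocated, consented, eligible and with a baseline.
4. Clarify that the blinding statement covers the two app versions only.

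These changes need wording, two further covariates and counts by arm. Their price is a weaker wait-list claim.

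Allocating after registration would remove the problem for later entrants, and Table 1 gives all three groups the same registration content. However, in the app arms registration takes place in the app that has already been downloaded, and recruitment is under way. The change would mean reworking the entry route and would leave two enrolment procedures in one trial. It is preferable only if the sponsor finds it feasible, and it is not required.
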